#### Music therapy

In music therapy, participants are taught to use music to express themselves, reduce stress, and cope with daily challenges. Existing literature suggests music therapy benefits social, cognitive, motor, and emotional/psychological functioning in healthy older adults and patients with neurological disorders [4, 7, 14]. NIH has endorsed exploring the use of music therapy in brain disorders of aging [15]. Music therapy sessions are administered by a clinical music therapist.

#### Nutrition and culinary medicine

This educational intervention teaches cooking skills and how different foods can promote or inhibit healthy cognitive aging. ​The MINDS diet is similar to the MIND diet (i.e., encouraging plant-based foods and limiting foods concentrated with sugar or saturated fats), but emphasizes reducing consumption of red meat and other inflammatory foods, and adding Greek yogurt. Adherence to the MINDS diet will be tracked passively biweekly for the first 3 months and then monthly for the remainder of the study as part of the MINDS Study Activity Survey (see Table 1 for timing details). The survey results will be scored by one of the blinded investigators based on the MINDS diet daily checklist (Supplemental Material 3). A team of board-certified dieticians and American Culinary Federation certified chefs with years of experience in the healthcare industry will deliver these sessions.

**Table 1 Tab1:** Study schedule of enrollment and assessments. Collected data elements and their timing listed at the time of enrollment, allocation to either intervention or control, and post-allocation. All post-allocation time-points are relative to the time of enrollment, while enrollment occurs before allocation (represented by -t). Grey shaded cells with a checkmark (✓) indicate data collected through Cleveland Clinic Brain Study. All other cells with an ‘X’ indicate data collected through the MINDS study. The attendance survey and post-intervention feedback survey are only collected for participants in the intervention arm

	STUDY PERIOD					
	Enrollment	Allocation	Post-Allocation			
Timepoint	-t	0	Months 1–3	Month 3	Months 4–12	Month 12
**Enrollment**						
Qualifying risk factor	✓					
Reading score (WRAT-4)	✓					
Eligibility Criteria	X					
Informed Consent	X					
Allocation		X				
**Assessments**						
Clinical History and Examination	✓			X		✓
Blood sample	✓			X		✓
Stool sample	✓			X		✓
NP Testing	✓			X		X
ECG	✓					✓
Polysomnography	✓					X
EEG	✓					X
MRI	✓					X
Smell Test (UPSIT)	✓					✓
OCT Scan	✓					X
Questionnaires	✓			X		✓
MDS-UPDRS	X			X		X
MINDS Study Activity Survey		X	*Bi-weekly*		*Monthly*	X
**Intervention Arm Only**						
Attendance survey			*Weekly*			
Post-intervention feedback survey				X		

#### Cognitive skills

This intervention teaches participants cognitive compensatory strategies and more general psychosocial strategies to optimize brain health. Brain health strategies include mental engagement, social engagement, exercise, and stress management. Cognitive compensatory strategies are intended to mediate and accommodate for any cognitive difficulties (such as impaired working memory). These strategies may increase functional independence, reduce the impact of cognitive changes related to aging, and delay the onset and progression of neurological disorders [16, 17]. Sessions include group counseling led by a licensed neuropsychologist.

### Outcome measures

The primary outcome of the MINDS study is the progression in the clinicopathological features specific to the neurological disorder for which the participant has a risk factor. Progression criteria for each disorder are described in Table 2. The secondary outcomes include the appearance of inclusion criteria (see Table 2) for neurological disorders other than the one that led to their study enrollment and self-report questionnaires in the following domains: quality of life in neurological disorders, depression symptoms, anxiety symptoms, self-efficacy, stress, and global health (see Table 3 for details). Exploratory outcomes for this study are neurological disease-related genomic, proteomic, metabolomic, and gut microbiome RNA biomarkers collected at 3 time points. The schedule for all outcome measurements and other assessments is reported in Table 1. Multi-omics data to be explored in the study includes the following:

**Table 2 Tab2:** Inclusion and progression criteria by neurological disorder. Inclusion and progression criteria for each neurological disorder described

Neurological Disorder	Inclusion Criteria	Progression Criteria
Stroke	Moderate to severe white matter changes on MRI	Additional asymptomatic cortical infarct **Or** Further increase in white matter disease MRI changes **Or** Clinical stroke
Epilepsy	At least one epileptiform discharge (spike, polyspike, sharp wave) on overnight EEG	Increase in burden (per hour) of epileptiform discharges **Or** Electrographic seizure on EEG **Or** Clinical seizure
ADRDs	≤ 40 on subjective memory self-assessment on BACH **And** At least one memory task score (RAVLT Trial 7 or Total Score) to ≤ 1.5 SD below population mean	Increase in number of NP testing domain scores to ≤ 1.5 SD below population mean **Or** Drop in NP testing scores to ≤ 2SD below the mean **Or** Clinical diagnosis of dementia
Movement Disorders	Hyposmia (age and sex matched score ≤ 10th percentile) on the University of Pennsylvania Smell Identification Test (UPSIT)	> 4 points increase on modified MDS-UPDRS administered remotely **Or** Parkinson’s Disorder diagnosis **Or** Initiation of dopaminergic therapy

**Table 3 Tab3:** Self-report questionnaires. Self-report questionnaires and phenotypic domains

Domain	Questionnaire Name
Stress	Perceived Stress Scale (PSS-10)
Generalized anxiety symptoms	Generalized Anxiety Disorder 7 Item (GAD-7)
Depression symptoms	Patient Health Questionnaire Depression Scale (PHQ-8)
Self-efficacy	General Self Efficacy Scale
Quality of life related to neurological disorders	Neuro-QoL - Sleep Disturbance
	Neuro-QoL - Ability to Participate in Social Roles and Activities
	Neuro-QoL - Lower Extremity Function
	Neuro-QoL - Upper Extremity Function
General health	PROMIS (Patient-Reported Outcomes Measurement Information System) Global Health
Healthy activities related to aging	Healthy Aging Activity Engagement Scale

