**Methods and analysis:**

We present the Multidisciplinary lifestyle Interventions for Neurological Disorders during the Silent phase (MINDS) protocol, a randomized controlled trial of MLI in neurologically healthy older adults (≥ 50 years old) exhibiting elevated risk for common neurological disorders: stroke, epilepsy, Parkinson’s Disease, or Alzheimer’s disease and related dementias. Participants will be randomly assigned to intervention (*n* = 100) or control (*n* = 100) groups. The intervention group will receive 3 months of weekly 2-hour sessions on diet education, yoga, music therapy, and cognitive skills training. The participants’ neurological health and engagement in relevant lifestyle practices will be assessed at regular intervals for 12 months. Neuroimaging and samples for multi-omic analyses will be collected at baseline, and at 3 months and 12 months after enrollment. Primary outcomes will be signs of progression of the neurological disorder risk that qualified them for study enrollment or a clinical diagnosis of the disorder. Secondary and exploratory outcomes will be based on self-reported health and multi-omic data. Data analysis will include between-group and longitudinal within-group analyses.

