## Methods

### Aims of the trial

We aim to test the impact of MLI on neurological disorder progression in patients identified as at risk of stroke, epilepsy, PD, or ADRD associated with the a) transition from ‘at-risk’ preclinical (silent) stage to the worsening of clinicopathological changes or a diagnosis of a neurological disorder and b) the progression of pathological changes leading to the development of a neurological disorder. An additional goal of the MINDS study is to identify biomarkers that predict MLI’s efficacy in disease prevention or neuropathology progression in these patients.

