### Eligibility criteria

CCBS participants with increased risk of developing ADRD, PD, stroke, or epilepsy are eligible for the MINDS study. Risk factors for development of these disorders are based on the current available evidence (Table 2). These factors are not diagnostic for ADRD, PD, stroke, or epilepsy. The four neurological disorders show significant clinicopathological overlap, and a MINDS-eligible participant enrolled for stroke risk factors may develop dementia before a clinical stroke, or a participant enrolled due to risk of a neurodegenerative disorder may later develop seizures before the clinical manifestation of dementia. Study enrollment began in July 2023 and is expected to finish in December 2024.

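### A clinical diagnosis in a disorder other than the qualifying one is not itself a primary or a listed secondary event

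*Protocol article*

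**What the plan says.** Outcome measures defines the primary outcome as "the progression in the clinicopathological features specific to the neurological disorder for which the participant has a risk factor". The abstract (Methods and analysis) confirms the link to one disorder: "Primary outcomes will be signs of progression of the neurological disorder risk that qualified them for study enrollment or a clinical diagnosis of the disorder".

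For the remaining disorders one outcome is listed: "The secondary outcomes include the appearance of inclusion criteria (see Table 2) for neurological disorders other than the one that led to their study enrollment". The other secondary outcomes are self-report questionnaires (Table 3), and the exploratory outcomes are omic biomarkers.

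Table 2 has two columns per disorder. The inclusion column gives the marker that makes someone eligible; for stroke this is "Moderate to severe white matter changes on MRI". Clinical events appear in the progression column only.

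Two other places bear on this. Aims of the trial describes the transition from the silent stage to "the worsening of clinicopathological changes or a diagnosis of a neurological disorder" and, as a second part, "the progression of pathological changes leading to the development of a neurological disorder". Eligibility criteria notes overlap between the four disorders and says that "a MINDS-eligible participant enrolled for stroke risk factors may develop dementia before a clinical stroke"; it gives seizures in someone enrolled for neurodegenerative risk as a further example.

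**The concern.** The cross-disorder secondary outcome points to the inclusion column of Table 2, whereas the cross-disorder events that the protocol itself names, dementia and seizures, are in the progression column. Read as written, a participant enrolled for white matter changes who is diagnosed with dementia during the 12 months is a non-progressor on the primary outcome. The same participant reaches the secondary outcome only by newly meeting the memory-score criteria used for enrolment.

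At stake is whether the listed outcomes answer the first aim. Some of the clinically most important events that the trial could observe would enter no planned comparison between the arms.

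**Working it through.** **Step 1. What each column of Table 2 contains.**

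| Disorder | Inclusion column (what must appear for the secondary outcome) | Clinical or treatment events found only in the progression column |
|---|---|---|
| Stroke | Moderate to severe white matter change | Clinical stroke |
| Epilepsy | At least one epileptiform discharge on overnight EEG | Electrographic seizure; clinical seizure |
| ADRD | BACH subjective memory score ≤ 40 and a RAVLT score at least 1.5 SD below the mean | Dementia diagnosis |
| Movement disorders | UPSIT at or below the 10th percentile | Parkinson's diagnosis; start of dopaminergic therapy |

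No entry in the third column is also in the second. The progression column further holds subclinical changes (for example a new asymptomatic cortical infarct, or a rise of more than 4 points on the modified MDS-UPDRS), which are likewise outside the secondary outcome.

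**Step 2. How far the gap reaches.** There are four possible qualifying disorders, each with three others: 4 × 3 = 12 pairings. In each, a diagnosis in the other disorder is not primary (Outcome measures and the abstract) and not by itself secondary (inclusion column only).

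**Step 3. When the event is still captured.** It counts as secondary only if the marker newly appears at a scheduled assessment:

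- Dementia in someone enrolled on the stroke row needs both the BACH and the RAVLT criterion.
- A clinical seizure needs a discharge on the month 12 EEG.
- A clinical stroke needs moderate to severe white matter change on the month 12 MRI.
- A Parkinson's diagnosis needs a newly low UPSIT score.

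**Step 4. A marker already present at entry.** A marker that is there at baseline cannot newly appear. If a participant enrolled on one row also carries the marker of a second row, progression on the second row is outside the secondary outcome. Whether it is primary depends on the reading. The abstract and the secondary-outcome sentence speak of the single disorder behind enrolment. The phrase "progression in the clinicopathological features specific to the neurological disorder for which the participant has a risk factor" could be taken to cover each disorder for which a marker is held. The document does not say which reading applies.

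**Step 5. Set against the aims.** The aims speak of a neurological disorder without restricting it to the qualifying one, and Eligibility criteria says that another disorder may come first. The outcome list has no event that corresponds.

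**Step 6. What can be quantified.** The only design figure nearby is the 18% control progression rate in Sample size calculation, and it reproduces:

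- Odds ratio: exp(0.8 × π/√3) = 4.27.
- Control odds: 0.18/0.82 = 0.2195. Divided by 4.27 this is 0.0514, an intervention rate of 0.0514/1.0514 = 4.89%.
- With 90 per arm (180 analysed) and the two-proportion normal formula, the mean rate is 0.1145 and z = [(0.18 − 0.0489) × √90 − 1.96 × √(2 × 0.1145 × 0.8855)] / √(0.18 × 0.82 + 0.0489 × 0.9511) = (1.244 − 0.882)/0.441 = 0.82, a power of 0.794 against the stated 0.8.

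This figure concerns the primary outcome. No rate is given for events outside the qualifying disorder, so nothing further can be computed for them.

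**The case against.** The best defence is that a primary outcome specific to the qualifying disorder is a legitimate choice, and that the aims may use a neurological disorder as generic wording for the four rows. The overlap passage says only that cross-disorder events may occur, and the plan does respond to it with a secondary outcome. The verb that introduces the secondary outcomes leaves the list formally open, and clinical history and examination are scheduled at months 3 and 12, so a diagnosis would be recorded and could be reported. All of this stands as a defence of the primary outcome. It does not repair the secondary one, because no listed item captures the event. This is also not detail left to a fuller document: the article states the rule and ties it to the inclusion column.

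A second defence is that the markers precede disease. The eligibility text says that hyposmia predates a Parkinson's diagnosis by years in most patients, and that memory signs can show up to two decades before clinical dementia. On that account, however, someone diagnosed within 12 months may well have carried the marker at entry, and then it cannot newly appear. The argument helps only if the primary outcome covers every disorder for which a marker was held, which is the unsettled reading.

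A reader might infer more than the documents support:

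- *That progression of a second baseline risk factor certainly counts nowhere.* The wording is ambiguous, so this is a possibility and not a fact.
- *That the primary outcome must become an any-disorder composite.* Enrolment began in July 2023 and the trial is open-label, so redefining the primary outcome is a debatable trade-off. It would also give participants with more markers more routes to progression.
- *That counting these events would ease the event-rate problem.* Assume that a share q = 10–30% has a second marker and that r = 10–18% progress on it. Then 0.18 + q × r × 0.82 gives 0.188 to 0.224. Neither q nor r is in the documents, and any gain in power would need the same odds ratio on the added events; a weaker effect would reduce or reverse it.
- *That people with dementia would miss the BACH criterion through lost insight.* Nothing in the documents supports this.

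**Conclusion.** The point holds for the secondary outcome as written. In all 12 pairings, a clinical stroke, a clinical or electrographic seizure, a dementia or Parkinson's diagnosis, or a start of dopaminergic therapy in a non-qualifying disorder is neither primary nor, by itself, a listed secondary event. This rests on reading the outcome text and Table 2 literally and on no numerical assumption. The mismatch with the aims is clearest for the first part, which names diagnosis.

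How many participants are affected cannot be derived, and no claim about event rate or power follows. The treatment of a second risk factor present at entry is an ambiguity to be resolved and not an established loss. The point is worth acting on because the remedy is cheap and brings the listed outcomes into line with the stated aim.

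**What to change.** Leave the primary outcome unchanged. Reword the cross-disorder secondary outcome along these lines: *appearance of the inclusion criteria, or meeting any Table 2 progression criterion including a clinical diagnosis, for a disorder other than the one that led to enrolment.*

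Add one sentence stating whether, for a participant with two risk factors at baseline, the second disorder falls under the primary or the secondary outcome. The rewording captures such progression if it is placed under the secondary outcome. Settle both before any comparative data are examined.

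The cost is an amendment to the outcome text. Table 1 already schedules MRI, EEG, neuropsychological testing, UPSIT, MDS-UPDRS and clinical examination at baseline and month 12, and restricts none of them by qualifying disorder. The small downside is a more heterogeneous secondary outcome, since a new risk marker, a subclinical change and a clinical diagnosis would count alike. New risk markers and clinical diagnoses should therefore also be reported separately by arm.

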#### Data analysis plan

We will use a modified intention-to-treat population approach and include participants with valid baseline data and at least one post-baseline data point. Missing data among these participants will be handled using multiple imputations, clearly described, and with sensitivity analysis to test the robustness of the results.

Primary outcome analysis will be completed using a Fisher’s exact test to compare the proportions of progression in the intervention and treatment groups. To analyze secondary and exploratory outcomes between groups, we will use mixed-effects regression models to evaluate change in outcome as a function of group, time, and group-by-time interaction. We will also conduct longitudinal analysis within groups using repeated measures ANOVA to compare measures at time points, with covariates as fixed effects. Effect sizes and confidence intervals will be reported. Additionally, we will assess baseline sample characteristics and test for any baseline group differences using two-sample t-tests for continuous variables and Chi-square tests for categorical variables. We will also conduct an adherence analysis by reporting intervention session attendance rate and summary statistics for self-reported engagement with intervention domains and testing for any differences in these adherence metrics based on cohort number, age/sex, and other covariates. We will conduct sensitivity analyses aligned with best practices to see if the outcome analysis results are robust to any potential confounders, including baseline imbalance or intervention non-compliance.

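### The group-by-time mixed model assigned to all secondary outcomes does not fit the new-onset outcome, appearance of another disorder's inclusion criteria

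*Protocol article*

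**What the plan says.** The protocol article's Outcome measures section lists two kinds of secondary outcome. One is "the appearance of inclusion criteria (see Table 2) for neurological disorders other than the one that led to their study enrollment"; the other is a set of self-report questionnaires.

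The Data analysis plan reserves the comparison of proportions for the primary outcome: "Primary outcome analysis will be completed using a Fisher’s exact test to compare the proportions of progression". For the rest it states: "To analyze secondary and exploratory outcomes between groups, we will use mixed-effects regression models". These models are to describe change by group, time and their interaction. No exception is made for a binary outcome.

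Three of the Table 2 criteria rest on tests that Table 1 schedules at baseline and month 12 only:
- stroke: "Moderate to severe white matter changes on MRI"
- epilepsy: "At least one epileptiform discharge (spike, polyspike, sharp wave) on overnight EEG"
- movement disorders: "Hyposmia (age and sex matched score ≤ 10th percentile) on the University of Pennsylvania Smell Identification Test (UPSIT")

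The dementia criterion uses BACH and RAVLT. Both belong to the neuropsychological battery, which Table 1 also schedules at month 3. The abstract, however, lists neuroimaging among the month-3 collections, whereas Table 1 leaves the month-3 MRI cell empty.

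**The concern.** A criterion can only appear in someone who did not have it at entry. A new-onset variable is therefore zero at baseline in every participant, and a model of change from baseline has no baseline variation to work with. The analyst would have to choose a link, a coding or another method after seeing the fit fail, in an open-label trial.

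The stakes are moderate. This is one secondary outcome, but it is the only one built on disorder criteria and not on questionnaires. The Perspective section concedes that the progression rate needed for the primary outcome may not be reached, and it looks to the secondary outcomes for support.

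**Working it through.** **The plan's own figure.** For secondary outcomes, Sample size calculation states a detectable Cohen's f of 0.27 at power 0.8 and a 5% level, with 180 analysable. Taking λ = f²N = 0.27² × 180 = 13.12 and a noncentral F test with 5 numerator degrees of freedom gives power 0.796, so the figure reproduces. The 5 degrees of freedom (1 group, 2 time, 2 interaction) are my assumption; they correspond to three visits. With 1, 2 or 3 degrees of freedom the power would be 0.950, 0.906 or 0.866. The figure contains no event rate, so it says nothing about a binary outcome. The points below do not depend on it.

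**Illustration.** 90 per arm (180 analysable, 1:1 allocation). Assumed new onset by month 12: 20% control (18/90), 10% intervention (9/90). Baseline: 0/90 in both arms.

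1. *Logit link, new-onset coding.* Ignoring within-person correlation, the variance of the group-by-time log odds ratio is the sum of 1/count over the eight cells (arm × visit × yes/no). Both baseline yes cells are 0, so the sum is infinite. A random intercept does not help: the likelihood keeps rising as the baseline intercept falls and the time effect rises to offset it. A plain logistic fit shows the same. At 5, 10, 20 and 25 iterations the intercept was -6.6, -11.6, -21.6 and -26.6, and the interaction standard error 2.5, 29, 4,358 and 53,088.

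2. *Identity link, new-onset coding.* Interaction = (0.10 − 0) − (0.20 − 0) = -0.10. The fitted linear mixed model gives -0.10, standard error 0.053, with random-intercept variance about 0. The simple two-proportion formula gives √(0.2×0.8/90 + 0.1×0.9/90) = 0.053. The baseline rows contribute nothing.

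3. *Month-12 comparison of proportions.* Odds ratio (9/81)/(18/72) = 0.44. Standard error of its log: √(1/9 + 1/81 + 1/18 + 1/72) = 0.44. Risk difference -0.10, 95% interval -0.10 ± 1.96 × 0.0527, or -0.203 to 0.003.

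4. *Met/not-met status at each visit.* Suppose 20% in each arm already meet another criterion at baseline and none lose it (assumed). Month-12 prevalence is 0.20 + 0.80 × 0.20 = 0.36 in control and 0.20 + 0.80 × 0.10 = 0.28 in intervention. The eight-cell formula now gives a finite standard error of 0.49. But the odds ratio is (0.28/0.72)/(0.36/0.64) = 0.69 and the risk difference -0.08, where new onset among those free at baseline gives 0.44 and -0.10. With 10% or 30% at baseline the odds ratio is 0.60 or 0.75. The model fits, but it answers a different question. If findings could also disappear between visits, losses would be netted against gains.

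**Visits per criterion (Table 1).**

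| Criterion | Test | Month 3 | Month 12 |
|---|---|---|---|
| Stroke | MRI | no | yes |
| Epilepsy | EEG | no | yes |
| Movement disorders | UPSIT | no | yes |
| Dementia | BACH, RAVLT | yes | yes |

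Three of four have a single post-baseline visit. If the abstract's month-3 neuroimaging were correct, it would be two of four.

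**The case against.** The strongest reply is that the Data analysis plan names no link and no coding, that a condensed article may leave such detail to an analysis plan, and that the use of Cohen's f suggests the sentence was written with continuous scores in mind. The omission of link and coding would indeed be no finding. But the article does more than omit: it assigns one model to all secondary outcomes and reserves the comparison of proportions for the primary. A stated method and a stated outcome do not match.

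Four stronger readings are tempting, and the documents do not support them.

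- *The outcome cannot be analysed by the stated model at all.* That holds only for a logit link with new-onset coding. A linear model runs, and so does a logistic model of status at each visit if some participants meet a second criterion at baseline. That is possible: the Exclusion criteria do not bar it, and Eligibility criteria stresses overlap between the disorders.
- *The missing month-3 tests rule the model out.* Two visits are enough for a group-by-time term. The schedule only means that repeated measures add little.
- *The very large standard errors that software prints measure the damage.* They reflect when the iterations stop and nothing about the trial.
- *Participants who already meet a second criterion stay in the denominator as non-events and dilute the effect in proportion to their number.* The article does not say how they are counted. Each participant also has three non-qualifying criteria, so someone who already meets one can still acquire the other two. With equal, independent onset (assumed), overall rates of 20% and 10% imply 1 − 0.8^(1/3) = 0.0717 and 1 − 0.9^(1/3) = 0.0345 per criterion. For two remaining criteria the rates are 0.138 and 0.068, a difference of 0.070 and not 0.10. If 10% to 30% were affected (assumed), the risk difference would shrink by about 3% to 9%, roughly a third of the proportion affected.

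**Conclusion.** The point holds as a mismatch between a stated method and a stated outcome. With new-onset coding, the logistic group-by-time model yields no usable test and the linear one reduces to the month-12 risk difference (-0.10, standard error 0.053 under the assumed 20% and 10%). With status coding the model fits but targets change in prevalence; in the illustration the odds ratio moves from 0.44 to 0.69. The event rates and baseline prevalences are assumptions, but the conclusion about the logit link needs only that the baseline value is zero for everyone.

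The count of three criteria without a month-3 test follows Table 1 and is subject to the conflict with the abstract. The point touches one secondary outcome; the primary analysis and the questionnaires are unaffected. It should be corrected before analysis.

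**What to change.** - Take this outcome out of the mixed-model sentence. For each participant, count only non-qualifying criteria that were absent at baseline, which also settles how people with two criteria at entry are handled.
- Compare between arms the proportion with at least one new criterion by month 12, using Fisher's exact test or logistic regression, and report the risk difference with its confidence interval.
- Keep the mixed model for the questionnaires, which Table 1 schedules at baseline, month 3 and month 12.
- Reconcile the abstract with Table 1 on month-3 neuroimaging.

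The cost is one or two sentences in the analysis plan and a correction in one of the two schedule statements. No new data are needed.
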